# Cost-effectiveness of a screening strategy for Q fever among pregnant women in risk areas: a clustered randomized controlled trial

**DOI:** 10.1186/1472-6874-10-32

**Published:** 2010-11-01

## Abstract

**Background:**

In The Netherlands the largest human Q fever outbreak ever reported in the literature is currently ongoing with more than 2300 notified cases in 2009. Pregnant women are particularly at risk as Q fever during pregnancy may cause maternal and obstetric complications. Since the majority of infected pregnant women are asymptomatic, a screening strategy might be of great value to reduce Q fever related complications. We designed a trial to assess the (cost-)effectiveness of a screening program for Q fever in pregnant women living in risks areas in The Netherlands.

**Methods/design:**

We will conduct a clustered randomized controlled trial in which primary care midwife centres in Q fever risk areas are randomized to recruit pregnant women for either the control group or the intervention group. In both groups a blood sample is taken around 20 weeks postmenstrual age. In the intervention group, this sample is immediately analyzed by indirect immunofluorescence assay for detection of IgG and IgM antibodies using a sensitive cut-off level of 1:32. In case of an active Q fever infection, antibiotic treatment is recommended and serological follow up is performed. In the control group, serum is frozen for analysis after delivery. The primary endpoint is a maternal (chronic Q fever or reactivation) or obstetric complication (low birth weight, preterm delivery or fetal death) in Q fever positive women. Secondary aims pertain to the course of infection in pregnant women, diagnostic accuracy of laboratory tests used for screening, histo-pathological abnormalities of the placenta of Q fever positive women, side effects of therapy, and costs. The analysis will be according to the intention-to-screen principle, and cost-effectiveness analysis will be performed by comparing the direct and indirect costs between the intervention and control group.

**Discussion:**

With this study we aim to provide insight into the balance of risks of undetected and detected Q fever during pregnancy.

**Trial registration:**

ClinicalTrials.gov, protocol record NL30340.042.09.

## Background

Q fever, a zoonosis caused by *Coxiella burnetii *(*C. burnetii*), primarily infects ruminants and rodents [1]. Especially pregnancy products of infected animals like placentas and amniotic fluid can contain high numbers of bacteria. After drying, the organism spreads in aerosols and remains virulent for months. Humans are infected by inhalation of these contaminated aerosols. Most of the infected patients are either asymptomatic or present with a mild flu-like illness. However, Q fever may pose a serious threat to certain groups at risk, including pregnant women, immune compromised hosts and individuals with pre-existing cardiac valve or vascular defects [1,2]. In The Netherlands, the number of human cases of Q fever has dramatically increased from around 12 cases each year before 2007 to more than 2300 cases in 2009 [3-5]. This observation has led to several meetings of the Dutch Outbreak Management Team (OMT) of the Ministry of Health to curb the epidemic. Studies revealed that the epidemic among Dutch inhabitants was a result of Q fever outbreaks on dairy goat farms [6].

Pregnant women are by far the largest risk group in size. When infected by *C. burnetii*, most pregnant women will remain asymptomatic: percentages up to 90% have been described compared to 60% in the general population [7,8]. Notably, serious complications due to Q fever seem to occur more frequently during pregnancy if the infection is undetected and untreated. Pregnant women have an increased risk to develop chronic Q fever or to reactivate a past infection [9,10]. Furthermore, obstetric complications related to *C. burnetii *infection have been described. A landmark study from France showed obstetric complications including spontaneous abortion, preterm delivery, intrauterine growth restriction, oligohydramnios and fetal death in 81% of the 53 women who were positive for Q fever and not sufficiently treated with antibiotics [10]. However, because of the retrospective design selection bias might have led to overestimation of the complication prevalence. In a Canadian cohort study in an affected area, 3.8% of parturient women had evidence of previous exposure to *C. burnetii*. These women had higher risks for adverse obstetrical outcome in terms of premature delivery and prior or current neonatal death [11]. Little is known about the chances of vertical transmission from mother to child. Transmission across the placenta, transmission by inhalation of infected amniotic fluid or by ingestion of infected milk cannot be excluded.

Because most infected pregnant women remain asymptomatic, one of the suggested measures to prevent obstetric complications and maternal chronicity concerns a screening strategy. However, because of lack of information on the prevalence during pregnancy and lack of randomized controlled trials weighing potential benefits and risks associated with screening, evidence for its potential impact is scarce. The Health Council of The Netherlands therefore advised the Ministry of Health in 2008 to facilitate studies to inform decision makers. We therefore designed a trial to assess the effects of a screening policy for Q fever in pregnant women from areas with large numbers of Q fever cases on the pregnancy outcome and cost-effectiveness from a societal and health care perspective. The study will primarily provide insights into the balance of risks of undetected and detected Q fever during pregnancy.

## Methods/Design

Since ethical issues surrounding randomization of the individual pregnant woman for a Q fever screening or non-screening strategy could seriously threaten approval by an ethics committee, we designed a clustered randomized controlled trial in which primary care midwife centres are randomized to recruit either pregnant women for the control group or for the intervention group. In this way, the choice for either strategy by individual eligible women was avoided. Timing and phasing after eligibility checks are shown in figure 1. The study will be conducted according to the principles of the Declaration of Helsinki. The study protocol is approved by the Medical Ethical Review Board of the University Medical Centre Groningen. The study protocol is registered at http://ClinicalTrials.gov, protocol record NL30340.042.09. The inclusion of participants started in April 2010.

**Figure 1 F1:**
[figure not shown]
**Timing and phasing of the study**.

The conduct of the trial is currently supported by the Royal Dutch Society for Midwifery (KNOV), the professional organization of midwives. Midwife centres in risk areas for Q fever (incidence in 2009 of more than 50:100,000 inhabitants according to the National Institute for Public Health and the Environment (RIVM)), were primarily invited to facilitate inclusion of participants. During spring 2010 we expanded the area based on the incidence of 2010. All obstetricians, paediatricians, medical microbiologists and pathologists in these areas were informed about the study.

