### Randomization procedure

Participating midwife centres are randomized to include either pregnant women for the control group or for the intervention group. Randomization is stratified according to the risk of contracting a *C. burnetii *infection as determined by the number of goat farms in the neighbourhood (registration by Statistics Netherlands (CBS)), and by the size of the midwife centre.

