### Sample size calculation and statistics

Based on the literature and pilot data from The Netherlands, we expect that 12% of pregnant women in the high-risk areas will have serological evidence for a Q fever infection [17,18]. Of these women, we conservatively estimate that 25% will develop complications, so 3% of women will have the primary outcome. Assuming a reduction of the complication rate of 50% by early detection with screening during pregnancy, we will need a participation of at least 3,400 participants with complete follow up (statistical power of 80 percent, p ≤ 0.05). Assuming a loss to follow up of 10% and to allow for a small clustering effect, we aim to include 4,000 participants.

Data will be analyzed according to intention-to-screen principles. A two-sided p-value of 0.05 or less will be considered to indicate statistically significant. Descriptive statistics concerning the distributions of the predictor variables and outcome variables will be performed using the software SPSS for windows (version 16). For univariate analysis the chi-square test and Fischer's exact test will be used to compare proportions. For variables with a normal distribution, differences will be analysed with Student's t-test. In case of non-parametric distribution, differences between populations will either be evaluated using the Mann-Whitney-U test or the data will be log-transformed to obtain a normal distribution. Relative risks as well as absolute risk reductions and numbers needed to treat will be estimated with their corresponding 95% confidence intervals. Possible clustering of outcome data will be taken into account using generalised estimating equations (GEE) modelling.

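### Centres enter the trial on notified incidence but are randomised within goat-farm and size strata, so balance on incidence and on original versus added area is left largely to chance and the named analysis does not adjust for either

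*Protocol article*

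**What the plan says.** The Methods/Design section, in the text below Figure 1, defines the risk areas from which centres were first invited by "incidence in 2009 of more than 50:100,000 inhabitants according to the National Institute for Public Health and the Environment (RIVM"). It then adds: "During spring 2010 we expanded the area based on the incidence of 2010". No threshold or period is given for the 2010 figure. The same section states: "The inclusion of participants started in April 2010".

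Under Randomization procedure the unit is the centre: "Participating midwife centres are randomized to include either pregnant women for the control group or for the intervention group". Strata are formed by infection risk "as determined by the number of goat farms in the neighbourhood (registration by Statistics Netherlands (CBS)), and by the size of the midwife centre". Incidence and recruitment area are not among the strata. The article gives neither the number of centres nor how the added centres were allocated.

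Under Sample size calculation and statistics, one prevalence drives the calculation: "we expect that 12% of pregnant women in the high-risk areas will have serological evidence for a Q fever infection". A quarter of these women are expected to have complications, which gives 3% of all women, and screening is assumed to halve that. The target is 3,400 women with complete follow-up, raised to 4,000 for 10% loss and a small clustering effect. Clustering is to be handled by GEE. No area, incidence or stratum term is named.

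**The concern.** The plan uses two measures of the same risk. Notified incidence decides which centres may enter, and goat-farm number decides what is balanced. The Background section attributes the epidemic to outbreaks on dairy goat farms, so a farm count is a sensible marker. A count of registered farms does not, however, show by itself which of them had an outbreak, so the strata protect balance on actual infection pressure only in part.

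This matters because the sample size rests on events among all women, and an event requires a seropositive woman. If seroprevalence differs between original and added areas, an uneven split of added centres between the arms moves the expected number of events without any effect of screening. The same difference adds between-centre variance, which widens the GEE confidence interval when it is not modelled. The allowance for clustering is small, so there is little room to absorb it.

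**Working it through.** **1. The plan's own figure.** Inputs from the sample size section: 3.0% v 1.5%, two-sided 0.05, power 80%. Equal allocation is assumed. The two-proportion formula with continuity correction gives 1,664 per arm, 3,328 in total, within 3% of the stated 3,400. Without the correction it gives 3,068.

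**2. Room for clustering.** 4,000 x 0.9 = 3,600 completers. 3,600 / 3,400 = 1.06.

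**3. How uneven could the split be?** Assumptions, not in the document: J = 40 to 100 centres, a share s = 20% to 50% of them in the added area, equal allocation, existing strata ignored. The between-arm difference in added-area share has mean 0 and

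SD = sqrt(4 s(1 - s) / (J - 1)).

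- J = 100, s = 0.2: sqrt(0.64 / 99) = 0.08.
- J = 40, s = 0.5: sqrt(1 / 39) = 0.16.

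By simulation, the 95th percentile of the absolute difference is 0.15 to 0.30 over this range. Differences of 10 to 20 points are therefore plausible. Goat-farm strata would reduce them to the extent that farm count tracks incidence.

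**4. What such a split does to events.** Assumptions: seroprevalence 12% in original areas and p = 3% or 6% in added areas. With added share s in an arm:

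arm seroprevalence = 0.12(1 - s) + p s.

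| Added share, arm A v arm B | p | Seroprevalence A v B | Relative shift |
|---|---|---|---|
| 15% v 25% | 6% | 11.10% v 10.50% | 5% |
| 15% v 25% | 3% | 10.65% v 9.75% | 8% |
| 10% v 30% | 6% | 11.40% v 10.20% | 11% |
| 10% v 30% | 3% | 11.10% v 9.30% | 16% |

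At a 25% complication rate the shift is 0.25 x (0.12 - p) x difference in share. It runs from 0.25 x 0.06 x 0.10 = 0.15 percentage points to 0.25 x 0.09 x 0.20 = 0.45 percentage points. That is 10% to 30% of the planned 1.5-point difference. The sign is random, and the average over randomisations is zero.

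**5. Precision.** With s = 0.20 and the same prevalences, the area difference alone contributes

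ICC = s(1 - s)[0.25(0.12 - p)]^2 / [P(1 - P)],

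where P is the overall event rate.

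- p = 6%: P = 0.027, ICC = 0.000036 / 0.02627 = 0.0014.
- p = 3%: P = 0.0255, ICC = 0.000081 / 0.02485 = 0.0033.

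With 4,000 women in 100 to 40 centres there are 40 to 100 women per centre. The design effect 1 + (m - 1) ICC then runs from 1 + 39 x 0.0014 = 1.05 to 1 + 99 x 0.0033 = 1.32, against the 1.06 available. Modelling the area difference removes this component. Modelling the goat-farm strata would remove part of it.

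**The case against.** The strongest reply is that randomising centres already balances incidence and area in expectation. What remains is sampling variation between clusters, which a confidence interval from a correct GEE analysis covers. This stands, and it rules out calling the problem a bias. It does not remove the loss of precision, or the value of a prognostic term fixed in advance.

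Second, goat-farm count is reasoned, and notified incidence is imperfect too: the Background section puts asymptomatic infection at up to 90% in pregnant women and 60% in the general population, so notifications miss many infections. This also stands. An entry threshold and a stratification factor need not be the same variable, and the farm strata give some protection. It does not follow that they give full protection.

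Third, covariate adjustment and the allocation of late centres may be described in a full protocol or SAP that is not shown. That is fair, so the absence of a term from the article is not itself the fault. The point is narrower: the article reports a changed catchment, fixes the strata and sets a thin clustering allowance, and a useful safeguard is available.

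Some stronger inferences are tempting but unsupported:

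- **That the arms are unbalanced on area.** Only enforced balance is missing. Added centres randomised as a separate batch could already be roughly balanced.
- **That the 2010 incidence is on a different scale, or that added centres recruit later.** The article gives no period or threshold, the rate could have been annualised, and the order of the expansion and the April start is not stated.
- **That the 12% belongs to the 2009 area only, so that the 3% event rate must fall.** The text ties the 12% to high-risk areas in general, citing literature and pilot data. Its use for original areas above is an assumption made for illustration.

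**Conclusion.** The point holds as a modest weakness in design and analysis. It is neither a contradiction between sections nor a source of systematic error. Balance on incidence and on original-versus-added area holds in expectation and is only partly protected by the goat-farm strata. Under the stated assumptions the chance shift in expected events is about 5% to 16% in either direction, which is small beside the planned 50% reduction but not negligible where the clustering margin is about 1.06. The figures depend on a 6- to 9-point gap in seroprevalence and a 10- to 20-point difference in added-area share. Neither comes from the document. If prevalence is similar in the two areas, or farm count tracks incidence closely, the effect shrinks towards zero. The stated sample size reproduces and is not in question here.

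**What to change.** Prespecify the primary GEE model with the randomisation strata (goat-farm number and centre size) plus one centre-level term the trial already holds: either recruitment area (original v added) or the centre's notified incidence. Do not include both. Added centres are broadly those outside the 2009 rule, so the two terms largely duplicate each other, and planned events are few: about 1,700 x 3% + 1,700 x 1.5% = 77.

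Report seroprevalence and the primary result by area as a sensitivity analysis, and state how the added centres were randomised. If any added centres are still to be allocated, randomise them as their own stratum. This last step cannot help centres already allocated, so the model term is the main remedy.

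The extra term costs about one centre-level degree of freedom and no new data collection. Fix the choice of term before outcome data are seen.

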### Inclusion criteria

Pregnant women, 18 years of age or older, with an estimated date of delivery between June 1^st ^and December 31^st ^2010, and under supervision of a midwife in primary health care are eligible for inclusion. In The Netherlands, midwives working in primary health care are allowed to only supervise uncomplicated, singleton pregnancies. It is estimated that approximately 10,000 eligible pregnant women live in the Q fever affected areas.

### Exclusion criteria

Women who do not have access to internet and/or an email address are excluded because data collection is web-based. In addition, women who are unable to understand Dutch or to give informed consent, or who have previously been tested positive for Q fever are ineligible for participation into the study.

### Experimental procedure

#### Intervention group

Participants who are recruited by a midwife centre randomized for the intervention group are asked for a blood sample around 20 weeks postmenstrual age. If possible the visit is combined with the routine structural ultrasound scan around that time. If the participant is included after 20 weeks, the blood sample will be taken as soon as possible after inclusion. The sample will immediately be tested for antibodies against *C. burnetii *in the laboratory of the Jeroen Bosch Hospital which has analyzed most samples during the epidemic in 2007, 2008, and 2009. Serologic diagnosis of Q fever will be made by indirect immunofluorescence assay (IFA), the reference method for serodiagnosis of Q fever [12]. Both IgM and IgG antibodies against phase I and phase II antigens are measured according to the manufacturer's instructions (Focus Diagnostics, Cypress, CA, USA). Titres ≥ 1:32 are considered positive. All positive samples will be fully titrated to reduce the chance of treatment in false positives. In general, the first antibody to appear in acute Q fever patients is IgM phase II, followed by a more or less simultaneous IgG phase II and IgM phase I response and subsequent appearance of IgG phase I antibodies (see figure 2) [13]. This time-dependent serologic profile allows us to discriminate between a recent acute infection, a past infection, and a chronic infection. If the pregnant woman does not have evidence for an acute, past or chronic Q fever infection, standard care will be provided.

**Figure 2 F2:**
[figure not shown]
**Idealised antibody responses in acute Q fever as measured by IFA^13^**.

In case of acute Q fever, the participant will be referred to an obstetrician, and treatment will be advised according to the local hospital protocol. In the literature, the first choice treatment of Q fever during pregnancy is oral cotrimoxazole (sulfamethoxazole/trimethoprim) for at least 5 weeks [10]. Antibiotic treatment, further obstetrical care and serological follow up will be supervised by the obstetrician in collaboration with the medical microbiologist. The current routine for pregnant women being treated for acute Q fever is to perform monthly blood analyses to detect the development of chronic Q fever. If the titres decline, the frequency of these controls is scaled down to once every two months during pregnancy, and at 3, 6 and 12 months after delivery. If chronic Q fever develops, treatment will be continued until the end of pregnancy followed by bactericidal treatment with doxycycline and hydroxychloroquine after delivery. In Q fever cases placentas will be collected for polymerase chain reaction (PCR) and histo-pathology.

If there is evidence for a past infection, no treatment is started. However, midwives will be advised to perform an extra serological analysis later in pregnancy to exclude reactivation.

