#### Control group

Participants who are recruited by a midwife centre randomly allocated to the control group will also be asked for a blood sample around 20 weeks postmenstrual age. These blood samples will be stored at -20°C, and analyzed for *C. burnetii *after delivery. In case of a positive test, the participant's general practitioner will be advised to perform an extra serological analysis to exclude chronic Q fever. Antibiotic treatment will be started if needed according to the local protocol.

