### Outcome measures

The primary endpoint is a maternal (chronic Q fever or reactivation) or obstetric complication (low birth weight, preterm delivery or fetal death) after the first trimester of pregnancy in Q fever positive women.

The secondary endpoints are direct and indirect costs of the screening program compared to costs of complications which could be prevented by screening. Furthermore, we aim to assess the course of infection in pregnant women, the accuracy of the diagnostic tests used for screening, histo-pathological abnormalities of the placenta of Q fever infected women, and side effects associated with treatment.

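### Chronic Q fever and reactivation, two of the five primary-endpoint components, are sought on different serology schedules in the two arms, so the composite risk ratio can be biased

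*Protocol article*

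**What the plan says.** Under Outcome measures, the protocol article states: "The primary endpoint is a maternal (chronic Q fever or reactivation) or obstetric complication". The obstetric part has three components (low birth weight, preterm delivery, fetal death), so the maternal part is two of five. The share of events expected to be maternal is not given.

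The Intervention group section classifies infection by antibody pattern: "This time-dependent serologic profile allows us to discriminate between a recent acute infection, a past infection, and a chronic infection". Follow-up then depends on arm and infection stage:

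- **Intervention, acute infection.** The routine for treated women is to "perform monthly blood analyses to detect the development of chronic Q fever". If titres decline, the frequency is "scaled down to once every two months during pregnancy, and at 3, 6 and 12 months after delivery".
- **Intervention, past infection.** No treatment is started, but "midwives will be advised to perform an extra serological analysis later in pregnancy to exclude reactivation". No test after delivery is described.
- **Control.** "These blood samples will be stored at -20°C, and analyzed for" *C. burnetii* after delivery. If the result is positive, the woman's "general practitioner will be advised to perform an extra serological analysis to exclude chronic Q fever". No second antenatal sample is described.

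Item 1 of Data collection takes its serological time points from the Experimental procedure section, so these schedules are the stated plan for collecting serology. Obstetric outcomes come from one post-delivery questionnaire used in both arms, completed by the midwife, or by the obstetrician for women referred to hospital.

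**The concern.** Allocation decides how often, when and for what a seropositive woman is retested. A woman with acute infection in the intervention arm has repeated antenatal looks for chronic Q fever, and a woman with past infection has an advised look for reactivation. A comparable control has neither. Her one further test comes after delivery, on advice, and is aimed at chronic Q fever.

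The count of maternal events therefore reflects testing as well as any effect of screening. Randomisation does not remove this, because the difference in testing follows from allocation. Intention-to-screen analysis carries it into the estimate, and generalised estimating equations deal with clustering, not with unequal measurement. The trial is meant to inform a national decision on screening, so a diluted benefit or an apparent harm produced by testing would matter.

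**Working it through.** **1. Schedules side by side**

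| Event | Intervention | Control |
|---|---|---|
| Chronic infection present at the 20-week sample | Detectable, read at once | Detectable, read after delivery |
| Chronic Q fever developing later in pregnancy | Monthly or two-monthly tests (treated acute cases) | No antenatal test |
| Reactivation after the 20-week sample | One advised antenatal test (past infection) | No planned assessment |
| Chronic Q fever after delivery | 3, 6 and 12 months (acute cases with declining titres); none stated for past infection | One advised test, no window stated |

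**2. Which post-delivery tests can count.** Due dates run from 1 June to 31 December 2010 (Inclusion criteria), and all data are to be available by the end of February 2011 (Discussion). Counting back from that date:

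- No 12-month test fits; the earliest would fall in June 2011.
- A 6-month test fits only deliveries up to about the end of August 2010.
- A 3-month test fits only deliveries up to about the end of November 2010.

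The usable asymmetry is mainly antenatal and early post partum.

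**3. The plan's own figure.** The inputs are 12% seropositive × 25% with complications = 3%, halved to 1.5%, two-sided 0.05 and 80% power. With 1:1 allocation (assumed), the two-proportion formula with continuity correction gives 1,664 per arm, or 3,328 in total, close to the stated 3,400. Without the correction it gives 1,534 per arm, or 3,068. The sample size is not at issue; it is the baseline for step 5.

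**4. Effect on the risk ratio.** The article gives no detection rates and no split of events, so the following are assumptions. Among seropositive women, the obstetric risk is o = 0.20 and the true maternal risk q = 0.08, independent of each other. The proportion of maternal events detected is d. Then:

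observed risk = 1 − (1 − o)(1 − q·d)

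With full detection this is 1 − 0.80 × 0.92 = 0.264, near the article's 25%.

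No effect of screening:

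- d = 0.9 intervention, 0.5 control: 0.2576 / 0.2320 = **1.11**
- 0.9 v 0.3: 0.2576 / 0.2192 = **1.18**
- 0.5 v 0.9: 0.2320 / 0.2576 = **0.90**

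Screening halves both risks (o = 0.10, q = 0.04; true ratio 0.136 / 0.264 = 0.515):

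- 0.9 v 0.5: 0.1324 / 0.2320 = **0.57**
- 0.9 v 0.3: 0.1324 / 0.2192 = **0.60**
- 0.5 v 0.9: 0.1180 / 0.2576 = **0.46**

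**5. Effect on power.** Let m be the maternal share of events and s the control detection relative to intervention (both assumed). The observed control rate is 0.03 × [(1 − m) + m·s], and the intervention rate is 0.015 under a true halving. With 1,700 per arm and no continuity correction, power is 84% at s = 1. At s = 0.5:

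| m | Control rate | Observed RR | Power | RR if no true effect |
|---|---|---|---|---|
| 0.1 | 2.85% | 0.53 | 77% | 1.05 |
| 0.2 | 2.70% | 0.56 | 68% | 1.11 |
| 0.3 | 2.55% | 0.59 | 58% | 1.18 |
| 0.5 | 2.25% | 0.67 | 36% | 1.33 |

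This table covers only under-detection in controls. The reverse case is in step 4.

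**The case against.** The strongest case against the point has four parts.

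*Serology is not the only route.* General practitioner files and a participant questionnaire one month after delivery, covering symptoms and potential long-term consequences, are used in both arms. The figure of up to 90% asymptomatic in the Background section concerns infected pregnant women, not chronic Q fever or reactivation specifically. This stands. A reader might infer that half the primary endpoint is silent and found only by serology; the text supports neither the half nor the only.

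*Part of the ascertainment is equal.* Both arms give a sample around 20 weeks, so chronic infection already present is detectable in both. This stands and confines the problem to later events.

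*The schedule contrast is weaker than it looks.* Monthly testing is described as routine for treated acute cases, so a control diagnosed clinically could receive it, and many of the post-delivery tests fall after the data date. Both limit the size. Neither supplies an antenatal look for controls whose infection goes unrecognised.

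*The article is condensed.* Case definitions and endpoint windows may be in the full protocol, and their absence here is no fault. That is fair, but the point rests on the sampling the article does describe. No definition can recover antenatal control samples that the plan does not draw.

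**Conclusion.** The point holds in a limited form. Two of the five named components of the primary endpoint are ascertained mainly by follow-up serology whose timing and intensity differ by arm, and reactivation after the 20-week sample has no planned assessment in controls.

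The direction is uncertain. Bias against screening is more likely, because antenatal looks occur in the intervention arm only. It could run the other way if women with past infection are tested after delivery mainly in the control arm. A reader might infer a known bias of known size; the documents support neither.

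The illustrative null risk ratios of 0.90 to 1.18 rest on the assumed 20% and 8% risks, on assumed detection of 30% to 90%, and on one detection rate per arm, although the schedule also varies by infection stage. The wider figures in the power table need a large maternal share. What is firm is the unequal schedule, and that the planned analysis does not remove its effect.

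**What to change.** 1. Pre-specify the obstetric composite (low birth weight, preterm delivery, fetal death) as the key supporting analysis of the primary endpoint. It is collected the same way in both arms and does not depend on the serology schedule.
2. Report chronic Q fever and reactivation separately by arm, with the number and timing of serological tests per woman.
3. State in advance that a conclusion on screening driven by the maternal components must be read in light of unequal testing.

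This needs only text in the analysis plan and tabulation of test dates. It adds no sample and leaves care and monitoring untouched. The supporting analysis has fewer events than the full composite, by the maternal share, and so less power.

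Two further changes may be tempting but should not be made. Removing in-pregnancy results would drop antenatal reactivation, a named component. It could also erase chronic cases found and treated before delivery, which would happen essentially only in the screened arm, so it would create a new bias in favour of screening. Requiring a fixed-window post-delivery sample would be a new trial procedure in both arms, and a late window would not fit the February 2011 data date for the last deliveries.
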